## Abstract

**Background:**

Nonalcoholic fatty liver disease (NAFLD) and type 2 diabetes (T2DM) are common chronic diseases. The coexistence of NAFLD and diabetes accelerates the progression of both and tends to induce bad prognosis. To date, lifestyle modification has been suggested as the first-line treatment for NAFLD patients. Some studies indicated that lifestyle modification could normalize glucose levels in newly diagnosed T2DM, but many individuals do not reach glycemic targets in practice using lifestyle modification alone. Considering the tight link between NAFLD and T2DM, metformin, a widely used drug in diabetic patients with a good safety profile, may be a possible treatment or control of NAFLD progression. There is no therapeutic consensus for the treatment of NAFLD patients with diabetes. Therefore, it is essential to elucidate the beneficial effects of lifestyle modification combined with metformin on glucose-lipid metabolism in the NAFLD population with newly diagnosed T2DM.

**Methods:**

Participants will be recruited in this single-center, randomized clinical trial through telephone interview. All participants will be assigned randomly at a 1:1:1 ratio to three groups and treated with lifestyle modification including calorie-restricted dietary and exercise therapy, 500–2000 mg/day metformin, or treated with both lifestyle modification and 500–2000 mg/day metformin (the co-intervention group) for 12 weeks. The primary outcomes are changes in glycemic control and severity of fatty liver from baseline to 12 weeks of follow-up.

**Discussion:**

This trial is designed to clarify whether lifestyle intervention combined with metformin has synergistic effects on glycemic control, attenuating the progression of NAFLD in NAFLD patients with newly diagnosed T2DM.

**Trial registration:**

ChiCTR2300072031. Registered on 31 May 2023.

**Supplementary Information:**

The online version contains supplementary material available at 10.1186/s13063-025-09191-0.

## Administrative information

Note: The numbers in curly brackets in this protocol refer to SPIRIT checklist item numbers. The order of the items has been modified to group similar items (see http://www.equator-network.org/reporting-guidelines/spirit-2013-statement-defining-standard-protocol-items-for-clinical-trials/).

## Introduction {6a}

Nonalcoholic fatty liver disease (NAFLD) is the most common chronic disease, with increasing incidence worldwide [1]. Available evidence indicated that NAFLD is closely associated with type 2 diabetes, most likely due to a common pathophysiological mechanism—insulin resistance [2]. A recent meta-analysis showed that patients with NAFLD have twofold higher increased risks of developing T2DM [3]. Similarly, more than 55% of patients with T2DM would develop NAFLD [4]. The coexistence of NAFLD and diabetes accelerates the progression of both and worsens hepatic and extrahepatic outcomes [5]. Thus, the early detection of NAFLD in newly diagnosed T2DM patients is of great clinical significance.

To date, there is no approved medication or surgery to treat NAFLD patients. Lifestyle could be the first-line intervention in patients with NAFLD. The efficiency of lifestyle modification on NAFLD has been elucidated in research [6]. Available evidence indicated that the biochemical remission of newly diagnosed diabetes is achievable through intensive lifestyle modification [7]. But the clinical intervention effects are inconsistent.

Metformin, as the first-line pharmacological therapy of T2DM, is prior to or in parallel with lifestyle modifications for the treatment of newly diagnosed diabetes. To our knowledge, metformin has been shown to have beneficial effects in alleviating hepatic lipogenesis in animal models of NAFLD. Zhang R. et al. revealed that metformin is effective in reducing body mass index (BMI), liver fat content, liver enzymes, and hemoglobin A1c (HbA1c) and improved insulin resistance in NAFLD patients with T2DM [8]. However, there are conflicting reports. In a prospective study, metformin was not associated with improvements in transaminase levels, hepatic fat content, and HbA1c [9]. Given the widely used metformin in diabetes patients, the beneficial effects of metformin treatment need to be further elucidated among NAFLD patients with T2DM. The objective of this randomized clinical trial is to test the efficacy of metformin as an adjuvant to lifestyle modification in improving glucose-lipid metabolism among NAFLD patients with newly diagnosed T2D.

### Objectives {7}

The primary objective of this randomized clinical trial is to evaluate the efficacy of lifestyle modification combined with metformin in NAFLD patients with newly diagnosed type 2 diabetes.

### Methods/design {8}

The study is a randomized, single-center, parallel group, superiority clinical trial. All patients who meet eligibility criteria are invited to this study and then assigned to different groups with a 1:1:1 allocation rate, receiving 12 weeks of follow-up.

## Methods: participants, interventions and outcomes

### Study setting {9}{15}

This randomized clinical trial will be conducted in Shunde Hospital of Southern Medical University, a tertiary hospital in Foshan, China. Participants will be recruited through healthcare centers and advertising in media. All subjects are the newly diagnosed diabetes with NAFLD. The study protocol was granted by the Ethics Committee of Shunde Hospital of Southern Medical University (reference number: KYLS20220615) and was registered at the Chinese Clinical Trials Registry (ID: ChiCTR2300072031) prior to the start of recruitment. Enrolment of participants commenced in June 2023. The study design flow diagram is presented in Fig. 1.

**Fig. 1 Fig1:**
[figure not shown]
The trial flow diagram

### Participant characteristics and eligibility criteria {10}

The inclusion criteria were as follows: (1) Men and women aged 18–65 years, (2) diagnosed with NAFLD, (3) newly diagnosed T2DM (diagnosed with T2DM within 3 years) and HbA1c ≤ 10.0%, (4) body mass index (BMI) > 23.9 kg/m^²^, and (5) all participants would provide written and oral informed consent before any testing. Exclusion criteria were as follows: (1) Habitual alcoholic intake (alcohol consumption > 30 g/day and > 210 g/week in men and > 20 g/day and > 140 g/week in women); (2) liver disease: ALT/AST thrice normal range, diagnosis of viral hepatitis, autoimmune liver disease, liver cirrhosis, and drug-induced hepatotoxicity; (3) the presence of one or more micro- and macrovascular complications of T2DM; (4) diseases that affect blood glucose levels (e.g., hyperthyroidism and hypercortisolism) or acute diabetic complications (e.g., ketoacidosis and hyperosmolar coma) or type 1 diabetes; (5) taking anti-fatty liver, anti-liver fibrosis drugs, drugs affecting glucose and lipid metabolism, and related health products; and (6) pregnant and lactating women.

### Who will take informed consent? {26a}

All subjects will be provided written informed consent before participating and then randomly assigned to three groups for a 3-month intervention. The informed consent will be collected by the treatment doctor.

### Additional consent provisions for collection and use of participant data and biological specimens {26b}

A voluntarily stool sample will be collected for analysis of intestinal flora for all subjects.

## Interventions

### Explanation for the choice of comparators {6b}

A lifestyle modification plays a fundamental role in the management of patients with newly diagnosed T2DM or NAFLD. However, many diabetic patients or NAFLD patients fail to achieve clinical goals in clinical practice. Metformin is the most common anti-hyperglycemic agent. The protective effect in chronic liver disease is controversial. We want to further clarify whether there is a synergistic reaction between lifestyle modification and metformin in NAFLD patients with newly diagnosed type 2 diabetes.

### Intervention {11a}

Participants will be randomly allocated to three groups according to the table of random numbers. Participants in the group of lifestyle modification receive a calorie-restricted dietary intervention (1200–1400 kcal/day for males, 1000–1200 kcal/day for females) and an exercise intervention including at least 150 min of moderate intensity exercise training per week. Participants in the group of metformin receive metformin at a dose of 500–2000 g/day and healthy education by the endocrinologist, and participants in the co-intervention group receive a calorie-restricted dietary intervention, an exercise intervention, and metformin treatment.

### Criteria for discontinuing or modifying allocated interventions {11b}

Potential adverse events mainly including hyperglycemia, hypoglycemia, and poor medication tolerance will be evaluated at the 2-week, 1-month, and 2-month phone call. Participants who refuse to contact researchers within 1 week or have severe adverse effects will be removed from the study.

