### Outcomes {12}

The primary outcomes are severity of NAFLD. The secondary outcomes include HbA1c, and homoeostasis model-insulin resistance index (HOMA-IR), an indicator of insulin resistance, will be calculated via formula as follows: [fasting glucose (nmol/L) × fasting insulin (mU/mL)/22.5], fasting blood glucose, 2-h postprandial blood glucose, BMI, waist circumference(WC), total cholesterol, low-density lipoprotein cholesterol, high-density lipoprotein cholesterol, triglycerides, and systolic and diastolic blood pressure.The primary and secondary outcomes will be reevaluated at the end of 12 weeks. Supplementary Table S1 presents the outcome definition.

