## Assignment of interventions: blinding

### Assignment of interventions: blinding {17a} {17b}

This trial is not blinded, so unblinding will not occur.

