### Methods in analysis to handle protocol nonadherence and any statistical methods to handle missing data {20c}

Data analysis will be performed according to the intention-to-treat principles. Per-protocol analyses will be done only for patients completing 12 weeks of therapy. Multiple imputation will be employed under the assumption of “missing at random.”

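### The removal rule in {11b} ends study participation, not only the intervention, so removed participants would enter the intention-to-treat analysis only through imputation under missing at random

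*Protocol article*

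**What the plan says.** Section {11b} of the Protocol article concerns the allocated interventions. It first describes safety monitoring: "Potential adverse events mainly including hyperglycemia, hypoglycemia, and poor medication tolerance will be evaluated at the 2-week, 1-month, and 2-month phone call". It then gives the rule: "Participants who refuse to contact researchers within 1 week or have severe adverse effects will be removed from the study". It does not distinguish stopping the intervention from ending follow-up, and it does not say whether removed participants are still assessed at week 12.

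On outcomes, section {12} says: "The primary and secondary outcomes will be reevaluated at the end of 12 weeks". The assessment sections {18a} agree: blood samples and the grading of fatty liver are planned at baseline and at 12 weeks.

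On analysis, section {20c} says: "Data analysis will be performed according to the intention-to-treat principles". It adds a completer analysis, "Per-protocol analyses will be done only for patients completing 12 weeks of therapy", and a missing-data method, "Multiple imputation will be employed under the assumption of" missing at random.

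The trial is open-label: "This trial is not blinded, so unblinding will not occur".

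**The concern.** Intention-to-treat depends on following randomised participants and analysing them in their arm, whatever their tolerance or adherence. A rule that takes people out of the study because of what happens to them on treatment works against this. Its effect is on data collection: an outcome that was never measured cannot be recovered by a later analysis plan.

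The removals may also be informative. The events named just before the rule are extremes of glycaemia and poor tolerance of medication. Severe forms of these could be related to the 12-week result that the participant would have had. Refusing contact may go with giving up the intervention. Because the trial is open-label, whoever judges severity can know the arm. If removal depends on the participant's own course in ways that baseline data do not capture, imputation from those who stayed can misstate an arm's mean change and hence the arm comparison.

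**Working it through.** **The sections side by side**

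1. {11b}: two triggers, refusal of contact within 1 week and severe adverse effects. The stated consequence is removal from the study.
2. {12} and {18a}: one post-baseline measurement of HbA1c and of fatty liver, at week 12. Someone removed earlier has neither, if the rule is followed literally.
3. {20c}: intention-to-treat with imputation under missing at random, plus a per-protocol analysis of 12-week completers. Removed participants belong to the first set, but their outcome values there would be wholly imputed.

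**Size**

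The plan gives no removal rate and no outcome for removed participants, so there is no figure of its own to reproduce. What follows is an illustration.

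Within an arm, let p be the share removed, R the mean change in those retained, and D the mean change in those removed minus R. The true arm mean is (1 − p)·R + p·(R + D) = R + p·D. If imputation recovers none of the deviation, it returns R, so the arm mean is off by p·D. For arms A and B, the true difference minus the estimated difference is

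pA·DA − pB·DB.

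With the same D in both arms this is (pA − pB)·D. The yardstick is the 0.4-point HbA1c difference in the sample size section {14}. The removal shares and D are assumptions:

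| Removed, A vs B | D = 0.5 | D = 1.0 | D = 1.5 |
|---|---|---|---|
| 20% vs 20% | 0 | 0 | 0 |
| 20% vs 5% | 0.15 × 0.5 = 0.075 (19% of 0.4) | 0.15 × 1.0 = 0.15 (38%) | 0.15 × 1.5 = 0.225 (56%) |
| 30% vs 10% | 0.20 × 0.5 = 0.10 (25%) | 0.20 × 1.0 = 0.20 (50%) | 0.20 × 1.5 = 0.30 (75%) |

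Swapping the arms reverses the sign. With 31 per group, 20% versus 5% is 31 × 0.20 = 6.2 against 31 × 0.05 = 1.55 people, so a handful of removals is enough to produce the middle row.

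**The case against.** Several points on the other side stand and limit the finding.

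- **Intention-to-treat is not abandoned.** A reader might infer that {11b} flatly contradicts {20c}. It does not: {20c} keeps non-completers in the main analysis through imputation and puts completers in a separate one. What remains is that the removed participants' contribution would rest on an untested assumption.
- **Loss of the 12-week data is a reading.** The rule stands under a heading about interventions, and the article condenses a fuller protocol. The literal wording nevertheless points to loss of follow-up, and nothing in the article corrects it.
- **The triggers are narrow.** A reader might infer that every case of hyperglycaemia or intolerance is removed, or everyone who is out of touch for a week. The listed events are ones to be evaluated at the calls. Only severe adverse effects and refusal of contact lead to removal, and the harms section {22} grades events as mild, moderate or severe. Some who refuse contact would also decline a week-12 visit.
- **Dependence on arm alone is compatible with missing at random** if arm is in the imputation model. The doubt concerns dependence on the participant's own unmeasured course. Adverse-event information from the calls could be used in the imputation and would reduce D. Such modelling detail is normally left to the analysis plan.
- **No direction can be claimed.** It is tempting to say that hyperglycaemia would remove people mainly from the lifestyle arm. No section supports this.
- **A one-arm figure must not be read as a treatment-effect bias.** Setting p·D for one arm against 0.4 is valid only if the other arm has no such deviation. The plan's 20% attrition allowance covers all causes and is not a rate for this rule.

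**Conclusion.** The point holds in limited form. A stated conduct rule, followed literally, leaves some randomised participants without a 12-week HbA1c or FibroScan result. The intention-to-treat analysis would then rest for them entirely on missing at random, which is doubtful when removal may follow glycaemic course or tolerance.

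Neither the size nor the direction of bias can be determined from the document. The shift is nil when removal and deviation are equal in the two arms. It is 0.075 to 0.225 HbA1c points, or 19% to 56% of the planned 0.4, under assumed removal of 20% versus 5% with D from 0.5 to 1.5. These figures assume that imputation recovers none of the deviation. They concern HbA1c only; nothing is quantified for the severity of NAFLD, which section {12} names as primary.

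**What to change.** Reconcile {11b} with {20c}:

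1. In {11b}, separate stopping the allocated intervention from leaving the study. This leaves unchanged when treatment is stopped.
2. State that all randomised participants who have not withdrawn consent are invited to the already planned 12-week blood tests and FibroScan.
3. In {20c}, state that they are analysed in their randomised arm with the observed data, and that only truly missing values are imputed.

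A delta-shift sensitivity analysis, which moves the imputed values of removed participants by a range of D, is an optional addition. It would be most useful for participants already removed.

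The cost is a few extra visits of a type already scheduled and an amendment communicated to the ethics committee, as section {25} foresees. The trial status section reports recruitment since June 2023, so outcomes of anyone already removed and past week 12 cannot be recovered.

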### Strategies to improve adherence to interventions {11c}

To facilitate adherence to the intervention, a WeChat group which contained endocrinologists and dietitians would be established for each subject to make daily follow-up. We provide online sports courses three times a week to strengthen exercise management.

### Relevant concomitant care permitted or prohibited during the trial {11d}

The concomitant treatment with drugs or nutrients that may affect glucose-lipid metabolism is prohibited during the trial. Subjects providing stool samples are advised not to take antibiotics or probiotics. In addition to the above, there are no restrictions.

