#### Hepatic steatosis

Transient elastography (FibroScan) would be performed after 8-h overnight fasting to assess hepatic steatosis and fibrosis according to liver stiffness measurements (LSM) and controlled attenuation parameter (CAP) score. The severity of fatty liver will be evaluated at baseline and 12 weeks later.

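### Minor: the on-study drug rule in {11d} is narrower than entry exclusion (5), so a liver-directed or anti-fibrosis agent without a possible glucose or lipid action is barred at entry but allowed after randomisation

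*Protocol article*

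**What the plan says.** Two sections of the protocol article govern other treatments.

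- **At entry**, under Participant characteristics and eligibility criteria {10}, exclusion (5) rules out patients "taking anti-fatty liver, anti-liver fibrosis drugs, drugs affecting glucose and lipid metabolism, and related health products".
- **On study**, under Relevant concomitant care {11d}, the rule is "The concomitant treatment with drugs or nutrients that may affect glucose-lipid metabolism is prohibited during the trial". Next comes advice for a subset: "Subjects providing stool samples are advised not to take antibiotics or probiotics". The section ends "In addition to the above, there are no restrictions".

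The liver is assessed by FibroScan, which is used to "assess hepatic steatosis and fibrosis according to liver stiffness measurements (LSM) and controlled attenuation parameter (CAP) score". On timing, the same section says "The severity of fatty liver will be evaluated at baseline and 12 weeks later". Outcomes {12} makes NAFLD severity the primary outcome and refers the reader to a supplement for detail: "Supplementary Table S1 presents the outcome definition". That supplement is not among the documents at hand. The blinding section states that the trial is open label.

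**The concern.** A bar on co-treatment at entry normally continues through follow-up for the same reason it was set: the listed agents could move the outcome. Here the entry list names liver-directed and anti-fibrosis drugs, and the on-study list does not. Because {11d} ends by lifting all other restrictions, the difference reads as permission and not as silence.

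What is at stake is the reading of the liver measurements. Patients using these agents at entry are excluded, so any use on study begins later. Its effect would fall within the change from baseline to week 12 and would be absent from the baseline value, so baseline adjustment in the planned ANCOVA could not remove it. Randomisation does not balance treatments started afterwards. With allocation known to participants and clinicians, uptake could differ between arms.

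**Working it through.** The plan gives no figure on this point, so the check is a class-by-class comparison of the two rules.

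| Class in exclusion (5) | Position under {11d} |
|---|---|
| Drugs affecting glucose and lipid metabolism | Repeated in full |
| Related health products | Covered in part, through nutrients that may affect glucose-lipid metabolism |
| Anti-fatty-liver drugs | Not named; caught only if they may affect glucose-lipid metabolism |
| Anti-liver-fibrosis drugs | Not named; caught only on the same condition |

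Count: 4 classes = 1 in full + 1 in part + 2 not named.

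**Are the unnamed classes covered by implication?** Partly. The test in {11d} is whether an agent may act on glucose-lipid metabolism. That is wide, and it will catch many anti-fatty-liver agents. It cannot be assumed to catch all of both classes, because exclusion (5) itself lists them separately from the glucose and lipid drugs. What remains is an agent aimed at the liver or at fibrosis for which no glucose or lipid action is suspected.

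**Does another section close the gap?** No. The discontinuation criteria {11b} concern adverse events and loss of contact. The adherence section {11c} describes messaging support and online exercise sessions. Neither carries the liver-drug exclusions past entry.

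**How could the result be affected?** Let p be the share of an arm that starts such an agent and d its mean effect on the 12-week change in CAP or LSM among users. The arm's mean change then shifts by p × d. For arms A and B the contrast shifts by

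p_A × d_A − p_B × d_B,

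which becomes d × (p_A − p_B) if the effect is the same in both arms. With equal uptake and equal effect the shift is zero. The between-arm comparison is therefore exposed only if uptake, or the effect among users, differs by arm. The article gives no value for p or d, so neither size nor direction can be calculated.

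**How many occasions exist to detect a start?** Under {11b}, adverse events "will be evaluated at the 2-week, 1-month, and 2-month phone call", which gives 3 calls. With the week-12 assessment there are 3 + 1 = 4 scheduled contacts.

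**The case against.** The best case for leaving the text alone has five parts.

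- **Breadth of the rule.** The prohibition covers suspected as well as established glucose or lipid action. The article names no agent that would escape it, and none that would move CAP or LSM within 12 weeks. This stands as a limit on size. It does not remove the mismatch in the written rules.
- **Different purposes.** Eligibility and on-study rules need not match word for word, and a condensed article may leave a prohibited-drug list to the full protocol. That would answer silence. It does not answer a sentence that states there are no further restrictions.
- **Low uptake.** Cirrhosis, viral, autoimmune and drug-induced liver disease and markedly raised transaminases are excluded. The Introduction says no drug is approved for NAFLD, and exposure lasts 12 weeks. The daily messaging contact in {11c} might also bring a new drug to light. All of this stands.
- **Same rule in every arm.** This stands too, and it is why harm needs a difference between arms. Open-label conduct makes such a difference possible; nothing in the article shows that it is likely.
- **Uncertain link to the primary outcome.** Whether LSM belongs to it depends on the supplementary table, which is not shown. CAP and LSM are in any case planned measurements, and the Discussion names steatosis and fibrosis as targets.

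Two stronger readings are tempting. A reader might infer that {11d} carries over only one of the four classes; that overlooks the partial cover of health products through nutrients. A reader might also call the permitted drugs a confounder of the primary outcome. Treatment begun after randomisation is an intercurrent event, not a baseline confounder, and the article gives no evidence that any bias has arisen.

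**Conclusion.** The point holds as a minor one. On their wording, the two rules differ, and the closing sentence of {11d} permits what exclusion (5) forbids for a narrow residue: liver-directed or anti-fibrosis agents without a possible glucose or lipid action.

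The consequence is a possible disturbance of the CAP or LSM comparison. It rests on three assumptions that the article neither supports nor rules out: that some participants start such an agent, that it alters the FibroScan readings within 12 weeks, and that its use or effect differs between arms. The expected size is low and cannot be quantified. Sample size, choice of test and analysis population are untouched. The case for acting is that the correction costs almost nothing.

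**What to change.** Reword {11d} along these lines: for the 12 weeks, anti-fatty-liver drugs, anti-liver-fibrosis drugs, drugs or nutrients with a possible effect on glucose-lipid metabolism (allocated metformin excepted) and related health products are not permitted; stool donors are asked to avoid antibiotics and probiotics; everything else is unrestricted.

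Add one question on newly started drugs and products to the three scheduled calls and the week-12 visit. Record any start of a listed agent as a protocol deviation, with the date and the arm. Keep the participant in the intention-to-treat analysis; the analysis section {20c} needs no change. If recruitment has already ended, recording such use still lets the sponsor report uptake by arm alongside the liver results.

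The cost is a revised paragraph, notice to the ethics committee if the change counts as a protocol modification, one extra question at contacts already planned, and a few more recorded deviations.
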